### Statistical analysis

We will use IBM SPSS Statistics 21.0 software to analyze the statistical data. Descriptive statistics, such as the number of patients with different ages, education levels, cancer stages and types of chemotherapy, as well as the percentage of patients in different groups relative to the total number of patients, will be calculated for different groups of demographic and clinical information. The mean and standard deviation will be used to compare the DMBQ total and dimensions scores, the SUPPH and FACT-B scores, and BMI. To compare the baseline balance between the two groups, two independent sample *t* tests, chi-square tests or Mann‒Whitney U tests, will be used, depending on whether the data distribution satisfies homogeneity of variance. The Shapiro‒Wilk test will be used to verify whether the scores of the two groups at different time points follow a normal distribution. If the data are balanced, repeated ANOVA will be adopted. Otherwise, we will use a generalized estimating equation (GEE) to analyze the intervention’s time, group, and interaction effects [36]. For all the above tests, *P* < 0.05 will indicate a statistically significant difference, the α level will be 0.05, and the tests will be two-sided. We will use intention-to-treat (ITT) analysis to minimize bias for sensitivity analysis [37]. The results of the last measurement of the patients who drop out of the study will be taken as the effect, which assumes that they complete the intervention, and the analysis will be reconducted with the GEE. Furthermore, missing data will be imputed with the mean values of the characteristics or with the help of multiple imputation methods if they are random and unrelated to the research elements.

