### Control group: usual care

The patients assigned to the control group will receive standard admission health education from the department. The main contents include the following: After the BC patients are admitted to the hospital, the doctor will ask about the patient’s condition and provide basic BC disease information. Nurses will distribute health education manuals, such as adverse reactions and coping methods related to chemotherapy. In addition, oncologists and nurses will provide clinical group lectures to explain the relationship between chemotherapy and diet, dietary information and strategies (mostly from the Dietary Guidelines for Chinese Residents, the World or American Guide, etc.), the necessity of weight management, etc. Health professionals will use face-to-face communication, question answering, demonstrations, and other methods during admission for chemotherapy to solve dietary problems. Patients who need food therapy will be evaluated by doctors and provided with relevant knowledge, precautions, indications and contraindications. During the home-based chemotherapy interval, telephone calls, WeChat messaging, online conferences, emails, and other forms of assistance will be provided to BC patients as needed. As is usual practice, no specific or individual recommendations will be provided.

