### Primary outcome

**Dietary management behavior.** The patient-reported Dietary Management Behavior Questionnaire (DMBQ) will be used to assess dietary management behavior in BC patients treated with chemotherapy. Our group members previously developed this questionnaire in 2023 based on the theoretical guidance of the ITHBC and the Capacity, Opportunity, Motivation-Behavior Model (COM-B) [33]. After conducting a scoping review to construct an item pool, three rounds of a multicenter survey were completed, including item selection and evaluation of the reliability, validation, and discriminative ability of the formal verified version. This tool comprises 4 domains and 22 items, including the adverse reaction coping (4 items), dietary information acquisition (5 items), dietary habit regulation (8 items), nutritional supplements, and dietary replacement (5 items) domains. The items are rated on a 5-point Likert scale ranging from ‘strongly disagree’ (1 point) to ‘strongly agree’ (5 points), with higher scores indicating better DMB. The structure was tested among 760 Chinese BC patients treated with chemotherapy from three hospitals. The total cumulative variance contribution rate of the 4 domains and the 22-item questionnaire was 62.67%, the Cronbach’s α coefficient was 0.908, the split-half reliability coefficient was 0.833, and the test-retest reliability coefficient was 0.938. Moreover, there were significant differences in the average scores of each dimension among patients with different ages, education levels, BMIs, menopausal statuses, and histological stages (all *P* < 0.05), and these differences were reflected in different pairwise comparison groups, indicating good reliability, validation and discriminative ability in BC populations.

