
In conclusion, this study will focus on the DMB of BC patients during chemotherapy. This study will establish an MDT to provide an early and comprehensive intervention to improve the nutritional status of BC patients and provide a basis for health management and quality of life for survival. A rigorous design will be used, guided by appropriate theory. Participants will be randomly assigned to two groups, and baseline characteristics will be assessed to determine any significant differences. The main questionnaire that will be used was developed with scientific steps and strict verification, which further ensures the rigor of the study design.

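### Baseline balance is to be judged by significance tests selected through a wrong rule (variance homogeneity); these tests cannot show balance, and a few prespecified covariates would serve the trial better

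*Protocol article*

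**What the plan says.** Four statements in the protocol article bear on this point.

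- **Purpose and choice of the baseline tests (Statistical analysis).** "To compare the baseline balance between the two groups", the section offers independent-sample t tests, chi-square tests or Mann-Whitney U tests. They "will be used, depending on whether the data distribution satisfies homogeneity of variance". P < 0.05, two-sided, applies to all tests. The closing paragraph of the Discussion presents the same step as part of a rigorous design: "baseline characteristics will be assessed to determine any significant differences".
- **Normality (Statistical analysis).** The Shapiro-Wilk "test will be used to verify whether the scores of the two groups at different time points follow a normal distribution". Its result is not named as the rule for choosing the baseline test.
- **Model (Statistical analysis).** "If the data are balanced, repeated ANOVA will be adopted"; otherwise GEE is used for "time, group, and interaction effects". The term balanced is not defined, and no covariate is named.
- **Factors related to the primary outcome (Primary outcome).** In the validation of the DMBQ, "there were significant differences in the average scores of each dimension among patients with different ages, education levels, BMIs, menopausal statuses, and histological stages", all with P < 0.05. Under Demographic and clinical information, age, education, BMI, menopausal status and cancer stage are among the variables collected, and Data collection places that questionnaire at every measurement, including T0.

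**The concern.** There are two errors of statement and one avoidable weakness.

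First, variance homogeneity does not separate the three tests. Marital status, work status or chemotherapy type have no variance to compare, and chi-square is used for them because they are categorical. For a score, the choice between t and Mann-Whitney rests on distribution or scale. If variances differ, the remedy is Welch's t. Mann-Whitney does not cure unequal variance, and under it does not test a difference in means.

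Second, a significance test of baseline asks whether a difference could be due to chance. In a properly randomised trial that is already known. A small P value is a chance event that invites an unplanned reaction, and a large one does not show that an imbalance is harmless. The sentence about balanced data follows in the same paragraph. If balanced means balanced at baseline, chance P values would choose the primary model.

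Third, the authors report factors associated with DMBQ dimension scores and will have them at T0. Adjustment named in advance handles chance imbalance in such factors; a baseline test does not.

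**Working it through.** **Inputs.** 44 per arm (Sample size; Randomization). Two-sided alpha of 0.05 (Statistical analysis). 13 baseline factors (Demographic and clinical information): nine demographic (age, BMI, marital status, children, education, income, living conditions, work, menopausal status) and four clinical (time of diagnosis, laterality, stage, chemotherapy type). The plan states no figure of its own on this point, so there is none to reproduce.

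**1. False flags under correct randomisation.**
- Expected number of P < 0.05: 13 × 0.05 = 0.65, whatever the correlation between factors.
- Probability of at least one, if independent: 1 − 0.95^13 = 0.487, about 49%.
- For the five factors named in the validation work alone: 1 − 0.95^5 = 0.226, about 23%.
- Some factors are related (age and menopausal status, for example), so the independent figure is a guide and not exact.

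**2. Differences that the tests pass over.**
- For an observed standardised difference d with n per arm, t = d × √(n/2).
- d = 0.4, n = 44: t = 0.4 × √22 = 1.876 on 86 degrees of freedom, P = 0.064. Not flagged.
- Smallest observed difference that is flagged: 1.988 / √22 = 0.424 SD.

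**3. Does passing the test protect the comparison?** This was checked by simulation: 200,000 trials, 44 per arm, no treatment effect, an unadjusted comparison at one time point, and one covariate explaining a share R² of outcome variance. R² is assumed, because the documents give none.

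| Baseline P of the covariate | Type I error, R² = 0.10 | Type I error, R² = 0.30 |
|---|---|---|
| All trials | 5.0% | 4.9% |
| P < 0.05 | 10% | 21% |
| P from 0.05 to 0.20 | 6.6% | 9.4% |

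Over all trials the error rate is correct. Given the imbalance that actually occurred it is not, and this also holds in the range that the plan would call balanced.

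**4. Where adjustment helps.** Write patient i's score at time k as group, time and group-by-time terms plus γx, where x is a fixed baseline covariate.
- Change from T0: γx − γx = 0. With T0 as a time level and complete data, the covariate drops out of every group-by-time contrast.
- Between-group level, or a post-baseline comparison: γx remains, so adjustment removes its variance and its chance imbalance.
- Numerical check (88 simulated patients, six time points, exchangeable GEE, one strong covariate): all five interaction estimates and their standard errors agreed to five decimals with and without the covariate. The standard error of the group coefficient fell from 0.297 to 0.210. The size of that fall reflects the simulated covariate strength and is no forecast for this trial.

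**The case against.** The strongest reply is that this is mostly a slip of wording. Normality is to be checked by Shapiro-Wilk, plausibly at T0 as well, so a sensible analyst would choose the right test. No action on a significant baseline result is stated outright. A covariate list commonly sits in a statistical analysis plan that is not shown, and the naming of three model effects does not say that nothing else will enter. Much of this stands. The absence of covariates is not in itself an error, and balanced may mean complete data and not baseline similarity. But the selection rule is stated, and a later document could repair it only by contradicting it. The baseline tests are also stated, twice.

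A reader might infer more than the documents support:

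- **That the validation factors drive the primary score.** The Primary outcome section reports differences between known groups in dimension scores, as evidence of discriminative ability. It gives no effect sizes, no result for the total score and no independent effects.
- **That unstratified allocation is a flaw.** It is valid and keeps the overall type I error at 5%. Stratifying on all five factors, even as binary variables, would give 2^5 = 32 strata and 88/32 = 2.75 patients per stratum.
- **That allocation should be stratified by department.** Oncology and breast surgery are both mentioned for recruitment, but controls "will receive standard admission health education from the department", described as one package, and no difference in care is shown. It would also need a new allocation scheme, since the present one ranks 88 numbers and splits them 44 to 44.
- **That adjustment is worth a fixed number of extra patients.** Such a conversion needs an R² that the documents do not give, and it does not apply to the interaction (step 4).
- **That the power of the baseline test to detect a true difference matters.** Randomisation excludes a true population difference at baseline. Only the observed difference is relevant (step 2).

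**Conclusion.** The point holds in a limited form. The test-selection rule is wrong as written. The baseline tests cannot show balance: there is about a 49% chance of at least one spurious flag over 13 factors if independent, while an observed difference of 0.4 SD (P = 0.064) goes unflagged. The validity of the randomised comparison is not in question. The harm would become material if a baseline P value decided between repeated ANOVA and GEE, which the text allows but does not clearly say.

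Naming covariates in advance is an improvement and not the repair of an error. Its gain lies in the between-group effect or a post-baseline comparison. Its size depends on how much DMBQ variance the covariates explain, which is unknown here. That the interaction gains nothing assumes T0 is a time level, data are complete and the covariate enters additively.

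**What to change.** 1. In Statistical analysis, delete the baseline significance tests together with the rule for choosing among them. Describe baseline by arm only: mean and SD, or counts and percentages. Amend the matching sentence at the end of the Discussion.
2. Define the term balanced in the sentence that chooses between repeated ANOVA and GEE, and state that no baseline P value decides the model.
3. Name a few T0 factors as fixed covariates in the DMBQ model, whatever balance is observed. Age, education and stage are an example. State which collected variable stands for stage, since the validation text speaks of histological stage and the data list of cancer stage.
4. State which effect the adjustment serves: the between-group effect or a post-baseline comparison, and not a group-by-time interaction that includes T0.

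The cost is wording only. The variables are already collected, and allocation and recruitment do not change. The downside is a few model degrees of freedom, depending on how categories are coded, out of 88 − 2 = 86 for a two-group comparison before dropout. The change should be made before any outcome data are seen by arm.

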**Methods:**

This single-blinded, single-center, randomized controlled trial will include 88 females who have not yet started the early or middle stage of the chemotherapy cycle. A random number table will be used randomly assign females to the intervention group or usual group at a 1:1 ratio. The intervention elements are based on the theoretical guidance of the Integrated Theory of Health Behavior Change (ITHBC). A multidisciplinary team (MDT) comprising oncologists, dietitians, nurses, traditional Chinese medicine (TCM) practitioners, and psychologists will provide the intervention. Intervention sessions will be conducted once a week for 8 weeks, beginning in the early or middle stage of the chemotherapy cycle and continuing through admission and a home-based interval chemotherapy period. The intervention includes face-to-face discussions, online meetings, WeChat messaging, and telephone calls. The themes target adverse reactions, dietary information and habits, self-care self-efficacy, treatment self-regulation, dietary supplement and TCM use, social support, weight management, and outcome expectations. The primary outcome is dietary management behavior measured by the Dietary Management Behavior Questionnaire (DMBQ). Secondary outcomes are self-care self-efficacy assessed by the Strategies Used by People to Promote Health (SUPPH); quality of life measured by the Functional Assessment of Cancer Therapy-Breast (FACT-B); and body mass index (BMI) measured by an electronic meter. All participants will be assessed at baseline and immediately, 1 month, 3 months, 6 months, and 12 months after the intervention.

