### Sample size

G power software will be used to calculate the sample size of the study, and ANOVA and a priori power analysis were selected [27]. Because there is little relevant literature and most multidisciplinary health management interventions do not report detailed sample size calculation parameters, we adopted system default parameters, including an effect size of 0.25, a power of 0.95, and an α of 0.05. After calculation, the total sample size was 72, with 36 participants in each group. Considering a 20% loss-to-follow-up rate, we obtained a final sample of 44 participants per group.

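### The main analysis switches between repeated-measures ANOVA and GEE on an undefined feature of the observed data; one prespecified baseline-adjusted model would end the choice and usually gain power

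*Protocol article*

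**What the plan says.** All of this is in the protocol article.

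- **Statistical analysis, preliminary tests.** "To compare the baseline balance between the two groups, two independent sample *t* tests, chi-square tests or Mann‒Whitney U tests, will be used". Then: "The Shapiro‒Wilk test will be used to verify whether the scores of the two groups at different time points follow a normal distribution".
- **Statistical analysis, choice of model.** The next sentences are "If the data are balanced, repeated ANOVA will be adopted. Otherwise, we will use a generalized estimating equation (GEE", and the GEE is used "to analyze the intervention’s time, group, and interaction effects". I take the ANOVA to have the same three terms.
- **Statistical analysis, missing data.** A sensitivity analysis carries the last measurement forward and refits the GEE. Mean or multiple imputation is also foreseen.
- **Discussion.** "Participants will be randomly assigned to two groups, and baseline characteristics will be assessed to determine any significant differences".
- **Abstract, Methods.** "The primary outcome is dietary management behavior measured by the Dietary Management Behavior Questionnaire (DMBQ"). The schedule has six assessments, T0 to T5: "All participants will be assessed at baseline and immediately, 1 month, 3 months, 6 months, and 12 months after the intervention".
- **Sample size.** "we adopted system default parameters, including an effect size of 0.25, a power of 0.95, and an α of 0.05", giving 72 in total (36 per group), raised to 44 per group for 20% loss.

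The article does not say what *balanced* means, whether T0 is a level of the time factor or a covariate, which of the three effects is the primary test, or what correlation between visits is expected.

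**The concern.** A primary analysis should be fixed before anyone sees outcome data. Here the rule for choosing it turns on a property of the data, and the property is not defined. Two analysts working from the same text could choose differently and report different P values for the DMBQ.

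There is also a cost in efficiency. If T0 is one of six outcome levels, the overall group effect is averaged over a visit at which randomised groups cannot yet differ, and the interaction spreads the effect over 5 df. The trial already collects T0 DMBQ, which could be used as a covariate.

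**Working it through.** **Step 1. What could *balanced* mean, and when would it be known?**

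| Reading | Settled by | Consequence |
|---|---|---|
| Groups similar at baseline | T0 tests by group | The stated GEE has only time, group and interaction, so it does not correct the imbalance that triggered it |
| Distribution acceptable | Shapiro–Wilk on scores at each visit | Outcome data are needed before the model is known |
| Complete data or equal numbers | Attendance through follow-up | With 20% loss planned, GEE would usually be used |

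On each reading the model is unknown until data are in hand.

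**Step 2. Do the two branches agree?** Simulation: complete data, six visits, 8,000 runs per setting, nominal 5%. The test is group-by-time, either by ANOVA without sphericity correction or by GEE with a robust Wald test and no small-sample correction. The article specifies neither detail, so both are assumptions.

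| Rejection rate with no effect | ANOVA | GEE |
|---|---|---|
| 36 per group, equal correlation 0.5 | 5.1% | 9.0% |
| 36 per group, AR(1) 0.7 | 7.7% | 9.0% |
| 44 per group, equal correlation 0.5 | 5.1% | 7.8% |
| 44 per group, AR(1) 0.7 | 7.6% | 8.1% |

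With a 0.5 SD effect, 36 per group and equal correlation 0.5, power for the same term was 51% (ANOVA) and 58% (GEE). The branches are not interchangeable.

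**Step 3. Power of the candidate tests.** The article states no power for any particular model. Its total of 72 does not follow from six visits: with f = 0.25, power 0.95 and an assumed correlation of 0.5, the group effect needs 124 and the interaction 28. That is a separate matter, and 72 is used here only as the evaluable number.

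Inputs: N = 72; d = 2 × 0.25 = 0.5 SD; two-sided 0.05 (Statistical analysis). Assumed: no difference at T0, the same d at T1–T5, and equal correlation ρ between all visits. Each noncentrality λ is worked at ρ = 0.5, with N/4 = 18.

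- Group effect over six visits: λ = (N/4)(5d/6)² / ((1+5ρ)/6) = 18 × 0.1736 / 0.5833 = 5.36; F(1, 70); power 63%.
- Interaction: λ = (N/4)(5d²/6) / (1−ρ) = 18 × 0.2083 / 0.5 = 7.5; F(5, 350); power 53%.
- Mean of T1–T5 minus T0, 1 df: λ = (N/4)d² / ((1+4ρ)/5 + 1 − 2ρ) = 4.5 / 0.60 = 7.5; F(1, 70); power 77%.
- Baseline-adjusted mean of T1–T5: λ = (N/4)d² / ((1+4ρ)/5 − ρ²) = 4.5 / 0.35 = 12.86; F(1, 69); power 94%.

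| Power, 36 per group | ρ = 0.3 | 0.5 | 0.7 | 0.8 |
|---|---|---|---|---|
| Group effect including T0 | 77% | 63% | 52% | 48% |
| 5-df interaction | 38% | 53% | 78% | 93% |
| 1-df change contrast | 63% | 77% | 94% | 99% |
| Baseline-adjusted mean | 94% | 94% | 98% | 99.7% |
| Variance ratio, change to adjusted | 2.40 | 1.71 | 1.33 | 1.20 |

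The second and third tests have the same λ, because (1+4ρ)/5 + 1 − 2ρ = 6(1−ρ)/5. The gap between them is therefore due to degrees of freedom alone. Only the step from the third row to the fourth comes from how baseline is handled.

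Simulation at ρ = 0.5 gave 62, 51, 77 and 94% for the four tests. Under AR(1) 0.7 it gave 64, 47, 63 and 86%. With 44 per group and ρ = 0.5 the formulas give 72, 63, 85 and 97.5%.

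**The case against.** **Balanced may mean complete data.** That is a normal use of the word, and the preliminary tests may then be only descriptive. This stands as a possible reading, but the choice still waits for the data.

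A reader might go further and infer that chance nearly decides the method. The 13 listed characteristics plus DMBQ, SUPPH and FACT-B make 16 baseline tests, and 1 − 0.95^16 = 56%. Twelve Shapiro–Wilk tests give 1 − 0.95^12 = 46%. The article does not support this. It never ties the switch to those tests, or to any one of them being significant. If baseline DMBQ alone decided, the chance would be 5%. Shapiro–Wilk rejections reflect non-normal scores, not randomisation, and both figures assume independent tests.

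**T0 as an outcome level is inferred.** True. Covariates and the primary contrast may sit in an analysis plan that is not shown, so their absence is not itself the fault. Nor does using T0 as an outcome cost power by itself: with a common baseline mean in both arms, essentially the same precision is recovered.

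**The power loss can be overstated.** Also true. Much of the gap to the interaction is its 5 df. Against the 1-df contrast the gain is 17 points at ρ = 0.5 but about 4 at 0.7. The only related figure in the article, the DMBQ test–retest coefficient of 0.938, is not a correlation between trial visits; at that value the variance ratio would be 1.05. A constant effect also favours averaging, and the Discussion wants the trend over time described.

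**Missing visits.** A reader might infer that ANOVA would simply discard patients with a missed visit. The section plans imputation and a carried-forward sensitivity analysis, so that does not follow. Whether those methods are sound is another question.

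**The analyst is to be blinded.** This limits steering towards one arm. It does not fix the method, since a two-sided P value is the same whichever arm is labelled which.

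**Conclusion.** The point holds for the switch. The article states a data-dependent choice of main analysis on an undefined criterion, and the two methods differ in error rate and power. If baseline imbalance is the trigger, the move to GEE does not correct it. This needs no assumption about correlation.

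The efficiency point is conditional on T0 being a time level, on a constant 0.5 SD effect and on equal correlation. At 36 per group, the baseline-adjusted mean beats the better of the two omnibus tests by 17 points at ρ = 0.3 (94 against 77%), 32 at 0.5 (94 against 63%, before rounding), 20 at 0.7 (98 against 78%) and 6 at 0.8 (99.7 against 93%). Against a 1-df change contrast the gain falls from about 31 points at 0.3 to under 1 at 0.8. A single figure for lost power would claim more than the article supports.

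**What to change.** 1. Delete the ANOVA/GEE switch, and state that neither baseline nor normality tests decide the method. Report baseline data descriptively.
2. Prespecify one primary model for all randomised patients: a linear mixed model for DMBQ total at T1–T5 with group, visit, group-by-visit and T0 DMBQ as covariate. An equivalent choice keeps T0 as an outcome with a common baseline mean in both arms.
3. Name one 1-df primary contrast, for example the group difference averaged over T1–T5. Without it the 94% does not follow: under a constant effect, group-by-visit over T1–T5 has no power beyond alpha.
4. Keep group-by-visit as a secondary analysis to describe the trend over time.
5. If a power gain is quoted, give it as a range over stated correlations.

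The cost is wording only. No visit, measurement or patient is added, and the named software can fit the model. The change should be dated before outcome data are examined by group, because afterwards it would itself look like a choice made from the data.

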### Study design

A prospective 8-week, two-arm, single-center, single-blinded parallel-group RCT with a pretest and follow-up will be conducted by an MDT. Female patients who are diagnosed with BC and waiting to start chemotherapy or who are in the early or middle stage of chemotherapy will be randomized to receive either usual dietary care or the multidisciplinary early dietary management intervention. The participants in the intervention group will receive the multidisciplinary early intervention measures constructed based on the ITHBC. In contrast, the control group will receive only the usual cancer dietary care education at admission and education manuals based on the Dietary Guidelines for Chinese Residents, the World or American Guidelines, etc. The intervention consists of the following eight themes, with sessions provide once per week: adverse reaction coping, dietary information and habit regulation, self-care self-efficacy training, treatment self-regulation training, dietary supplement and TCM use, social support seeking, weight management, and outcome expectation education. Detailed information is provided in Fig. 1. Eight intervention sessions will be provided throughout admission for chemotherapy and a home-based interval chemotherapy period. This intervention will be initiated during the early and middle stages of chemotherapy. Standard chemotherapy cycles include 4, 6, and 8 cycles. For example, for patients receiving 4 chemotherapy cycles, the first intervention session will be provided during the first or second admission for chemotherapy. For patients receiving 6 cycles, the first intervention session will be provided during the first, second, third, or fourth admission. For patients receiving 8 cycles, the first intervention session will be provided during the first, second, third, fourth, fifth or sixth admission. The duration of intervention sessions during different chemotherapy cycles is shown in Fig. 2. In addition to the baseline measurements, follow-up measurements were taken immediately after the end of the intervention (T_1_) and at 1 (T_2_), 3 (T_3_), 6 (T_4_) and 12 months (T_5_) after the intervention. T_1_ was measured immediately after the end of the eighth intervention session. T_2_, T_3_, T_4_ and T_5_ will be measured 30, 90, 180 and 360 days after the T_1_ measurement date, respectively. The intervention process is shown in Fig. 3. The same time points for follow-up in the intervention group will be also used for the control group.

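### With 72 to 88 patients, GEE run in its usual form tests the group-by-time interaction at about 8%, not the stated 5%; repeated ANOVA is affected only if an uncorrected F is read and sphericity fails

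*Protocol article*

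**What the plan says.** All references are to the protocol article.

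- **Software** (Statistical analysis): "We will use IBM SPSS Statistics 21.0 software to analyze the statistical data".
- **First choice:** "If the data are balanced, repeated ANOVA will be adopted".
- **Fallback:** "Otherwise, we will use a generalized estimating equation (GEE"), which is to analyse the "time, group, and interaction effects".
- **Sensitivity analysis:** dropouts keep their last measured value and "the analysis will be reconducted with the GEE". GEE will therefore be run whichever branch the main analysis takes.
- **Standard of evidence:** "the α level will be 0.05, and the tests will be two-sided".
- **Schedule** (Abstract, Methods): "All participants will be assessed at baseline and immediately, 1 month, 3 months, 6 months, and 12 months after the intervention". Study design adds that T2 to T5 "will be measured 30, 90, 180 and 360 days after the T_1_ measurement date".
- **Numbers** (Sample size; Randomization): 88 enrolled 1:1, with 36 per group (72) required before the 20% allowance for loss to follow-up.

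The article does not state the GEE covariance estimator, the test statistic, its reference distribution or the coding of time. For the ANOVA it names neither a sphericity correction nor the test line to be read.

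**The concern.** The trial asks whether dietary management behavior changes differently in the two arms. With one baseline and five later visits, the group-by-time interaction tests that directly, although the plan lists it beside the time and group effects without singling it out. Six visits in two arms give (6 − 1) × (2 − 1) = 5 degrees of freedom when time is categorical.

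A robust Wald test treats the estimated covariance of those five contrasts as if it were known. With 36 to 44 patients per arm it is not, and a chi-square reference allows nothing for that error. The test then rejects a true null more often than 5%. The excess would apply to the primary outcome and again to each secondary outcome analysed the same way. The carried-forward rerun would share the fault and so could not act as a safeguard.

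**Working it through.** **Inputs.** α = 0.05, six visits, n = 44 or 36 per arm (N = 88 or 72), all from the article. Assumed, because the article does not say: categorical time, robust covariance, Wald chi-square. The closed forms in steps 1 to 3 also assume normal data and complete rows. The article gives no type I error figure other than the nominal 0.05, so there is no calculated figure to reproduce.

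**1. GEE interaction test.** With complete data and a full group-by-time model, the robust Wald statistic is W = T² × n/(n − 1), where T² is the two-sample Hotelling statistic on the five visit contrasts. Under the null, T² × (N − 6)/(5(N − 2)) follows F(5, N − 6). The usual test rejects when W > 11.07, the 95% point of chi-square on 5 df. The true size is therefore

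P{ F(5, N − 6) > 11.07 × (n − 1)/n × (N − 6)/(5(N − 2)) }.

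- n = 44: 11.07 × 43/44 × 82/430 = 2.063; P{F(5, 82) > 2.063} = **0.078**
- n = 36: 11.07 × 35/36 × 66/350 = 2.030; P{F(5, 66) > 2.030} = **0.086**

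For an exact 5% test, W would have to exceed 12.48 (n = 44) or 12.84 (n = 36).

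Simulation (20,000 trials per setting, nine correlation structures) gave 7.7–8.0% at 44 per arm and 8.4–8.7% at 36. The result does not depend on the correlation. With 20% monotone dropout (4,000 trials per setting), 44 per arm at the start gave 8.3–8.4% and 36 per arm at the start gave 8.5–9.3%.

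**2. One-degree-of-freedom group effect.** By the same argument the size is P{F(1, N − 2) > 3.841 × (n − 1)/n}.

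- n = 44: 3.754 on (1, 86) df, 0.056
- n = 36: 3.735 on (1, 70) df, 0.057

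**3. Alternatives for the interaction.**

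- Multivariate (Wilks) test: exact for complete normal data; simulated 4.7–5.3%.
- Unstructured covariance with an F test on 5 and N − 2 df: size P{F(5, N − 6) > F₀.₉₅(5, N − 2) × (N − 6)/(N − 2)}. For n = 44, 2.321 × 82/86 = 2.213, giving 0.061. For n = 36, 2.346 × 66/70 = 2.212, giving 0.063.
- Generalized score test within GEE: simulated 4.6–4.8%.

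**4. Repeated ANOVA interaction, simulated.** The article gives no correlations between visits, so these are assumed. For correlations that decay with time, T0 to T1 is taken as about 56 days from the eight-week intervention.

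| Test read | True size |
|---|---|
| Uncorrected F, compound symmetry | 4.9–5.3% |
| Uncorrected F, decaying correlation (epsilon 0.91 down to 0.51) | 5.6–8.8% |
| Greenhouse-Geisser | 4.3–4.9% |
| Huynh-Feldt | 4.7–5.3% |
| Multivariate | 4.7–5.3% |

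Unequal spacing is not the cause. Under compound symmetry the uncorrected F holds its level whatever the visit dates. Correlation that decays by visit number, with the dates ignored, still gives 6.2–7.7%. What matters is non-sphericity left uncorrected.

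**The case against.** The strongest objection is that the article fixes only GEE and SPSS. The robust estimator, the Wald chi-square and categorical time are a reading of ordinary practice. A score test inside GEE would hold the level, and such settings are commonly left to a SAP, which is not shown. This stands as a condition on the result: the figures apply to GEE in its usual form, and the article does not say that this form will be used. It does not remove the point. The method, the effects to be tested, the sample size and the 5% standard are all stated, and the ordinary use of that method at that size does not deliver that standard.

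A reader might also infer that repeated ANOVA is above 5% on this schedule, or that every test in the plan misses its 5%. The documents support neither. The article never says that the uncorrected F will be read, gives no correlations, and names an analysis whose corrected and multivariate versions are sound. Silence on a sphericity correction is not an error in a condensed article. The one-degree-of-freedom group test is close to its nominal level.

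Finally, GEE is the fallback and the sensitivity analysis, the interaction is one of three listed effects, and the Discussion describes the study as preliminary and mainly about feasibility. This limits the weight of the point.

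**Conclusion.** The concern holds conditionally. With categorical time, robust covariance and a Wald chi-square on 5 df, the named GEE tests the interaction at 7.8% (88 complete patients) to 8.6% (72), which is 1.6 to 1.7 times the stated 5%. The carried-forward rerun, with up to 88 complete rows, sits at the 7.8% end. The excess is about 3 to 4 percentage points. It does not depend on the correlation between visits, but it does depend on those three unstated settings.

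The group effect is not materially affected. For repeated ANOVA, inflation of roughly 6 to 9% needs both an uncorrected F and non-spherical data, and the article establishes neither. Severity is minor to moderate.

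**What to change.** Name a small-sample test for the group-by-time interaction in the analysis section. Any one of these would do:

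- for complete data, the multivariate (Wilks) test;
- a REML mixed model with unstructured visit covariance and F tests with small-sample degrees of freedom, which also keeps patients with partial follow-up. The calculation above, with N − 2 denominator df, puts it at about 6%: better than the chi-square test, but not exact;
- if GEE is kept, a generalized score test, or a bias-corrected sandwich with an F reference.

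If the univariate repeated ANOVA is used, state that the Greenhouse-Geisser or Huynh-Feldt line will be read. Apply the same choice to the carried-forward rerun.

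The cost is a sentence or two of text and no extra patients or data. The downside is slightly larger P values and wider intervals.
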